**Study to assess safety and adherence of caretaker to prescribed treatment and advice (objective 5 & 8):**

The total sample size will be about 1200 patients in Dar es Salaam and 960 in Kilombero/Ulanga in the same randomised health facilities (total of 2160). The first half of all patients will be done 4 weeks after training and the second half one year after training to investigate the sustainability of the intervention effect overtime. The patients will be different than those included in the assessment of appropriate use of drugs and adherence, since the latter might be in more 'controlled' conditions than those included in this component, and less likely to have an unfavourable outcome.

**Subjects:** All voluntary patients between 2 months and 59 months coming to an outpatient facility in the study with a history of acute 'febrile' illness.

**Procedures:** Each child between 2 and 59 months brought to a clinic for acute care will be seen using the protocols implemented in that particular health facility (original IMCI or new paper chart or electronic IMCI protocol) as they would normally. The patient's caretakers will be asked whether they are willing to participate in a follow-up study. Those who agree will be read an informed consent script and asked to sign their consent. If a patient's caretaker agrees, a trained observer will be present to records details of the clinician's consultation and assess whether all procedures mentioned in the

IMCI protocol are adhered to or not. The diagnosis classification and treatment given will be recorded, as well as a cell phone number if available. The patient's caretaker will be asked to come back after 7 days, so that the child can be assessed for health outcome [cured, not cured (if not cured: worse, stable better)]. If not cured at day 7, they will be reassessed at day 14. A standardized form will be developed to record these observations. As is true in IMCI protocols, children's caretakers will be advised to come back to health facility in case the child is not better or gets worse after 1 or 2 days depending on severity of illness. They will be seen by dedicated staff and assessed clinically in case of unscheduled reattendance or readmission. Additionally we will use this opportunity to test the mothers' understanding of the diagnosis and treatment of the child and whether the prescribed treatment was in fact followed correctly.

**Outcome measures:** The primary outcome will be the rate of unscheduled reattendance and percent of caretakers who follow prescribed advice. Secondary outcomes will be the rate of patients cured at day 7, the rate of delayed complications and the rate of drug prescribed.

**Analytical plan:** outcomes will be compared between the two intervention groups (e-IMCI & paper IMCI) and the control one (C).

Similar design and procedures were used previously to assess the safety of not treating febrile children with a negative rapid test for malaria and proved to be quite feasible. The percentage of children followed-up was excellent (97%); the rate of unscheduled reattendance was 12% ([name] 2008b)

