If a patient's caretaker agrees, a trained observer will be present to records details of the clinician's consultation and assess whether all procedures mentioned in the IMCI protocol are adhered to or not. A standardized form will be developed to record these observations as well as the time for each encounter. In addition, following the usual consultation, the caretaker will be interviewed to assess comprehension of instructions regarding treatment and follow-up and a trained IMCI expert will repeat the patient assessment to compare the results of his/her formal IMCI assessment with that of the usual clinician. The expert will so determine the IMCI "gold standard" classification and treatment. If the expert feels that the safety of the child is compromised (e.g. diagnosis of pneumonia but no antibiotics prescribed), the expert will adapt the prescription (e.g. add anti-infective drugs). We have developed a set of indicators to assess whether a child is correctly assessed, classified, treated and counselled for use in the IMCI adherence study currently underway. These indicators are based on a very large scale multi-country supported by WHO in 2000 (Gouws, 2005) to assess the quality of care using IMCI compared with non-IMCI. For both observation and re examination phases of the study, the data collection tools will be adapted from the IMCI Multi Country Evaluation instruments ([http://www.who.int/imci-mce/Publications/HFS\\_instruments.pdf](http://www.who.int/imci-mce/Publications/HFS_instruments.pdf)).

**Outcome measures:** adherence to procedures in IMCI protocols, accuracy of diagnosis category, appropriateness of antimalarial and antibiotic prescription, , caretakers' understanding of advice.

**Analytical plan:** outcomes will be compared between the two intervention groups (new e-IMCI & new paper IMCI) against the control one (C).

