| R2: Training of clinicians for new IMCI paper and e-IMCI protocols in intervention arms | A.2.1: Training of clinicians                                         | I 2.1: Clinicians from intervention arms trained for new IMCI paper protocols and e-IMCI (12 months)    | CMOH (Dar es Salaam), IHI (K/U districts)                        |
| R3: Adherence and appropriate use of drugs                                              | A.3.2: Observation and assessment of 1920 patients consultations      | I 3.2: Diagnostic classification, appropriate prescription of antimalarials and antibiotics (30 months) | CMOH (Dar es Salaam), IHI (K/U districts)                        |
| R4: Safety of new IMCI algorithm                                                        | A.4.1: Follow-up of 2160 patients                                     | I 4.1: Unscheduled reattendance (24 months)                                                             | CMOH (Dar es Salaam), IHI (K/U)                                  |
| R5: Costs                                                                               | A.5.1: Costing of 300 children                                        | I.5.1: Cost (27 months)                                                                                 | CMOH (Dar es Salaam), IHI (K/U districts)                        |
| R6: Conference abstracts and papers                                                     | A.6.1: Analysis and writing                                           | I.6.1: Accepted abstracts and papers                                                                    | STI, IHI, CMOH                                                   |

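### The safety sample is kept apart from the adherence sample to avoid controlled conditions, yet its procedures put the same adherence-scoring observer in the consultation

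*Protocol*

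**What the plan says.** The protocol's safety study (objectives 5 and 8) enrols 2160 children who are to be different from the 1920 in the adherence study (objectives 3, 4 and 7). The reason given is that adherence-study children "might be in more 'controlled' conditions than those included in this component, and less likely to have an unfavourable outcome".

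The Procedures paragraph of the same section says that once the caretaker consents, "a trained observer will be present to records details of the clinician's consultation" and judges whether the IMCI steps are followed. The adherence-study procedures use the same sentence: "a trained observer will be present to records details of the clinician's consultation and assess whether all procedures mentioned in the IMCI protocol".

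Elsewhere, observation is tied to the adherence study only. Its sample-size paragraph describes the 1920 as observed consultations, and the task table in section 2.6 lists "A.3.2: Observation and assessment of 1920 patients consultations" for adherence but "A.4.1: Follow-up of 2160 patients" for safety. The safety outcomes are unscheduled reattendance and caretaker adherence (primary), then cure at day 7, delayed complications and drugs prescribed. Provider adherence is not among them.

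**The concern.** The reason for a second sample is that closer control of the consultation may make bad outcomes rarer. An observer who sits in the room and scores the clinician step by step is a form of such control. As written, field staff would apply it to the sample that was meant to be free of it.

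The safety claim is non-inferiority on unscheduled reattendance with an absolute margin of 5 percentage points. If observation lowers event rates, or shrinks the difference between arms, an excess in routine use could be missed. Section 2.5.2.5 justifies the control arm by the need to detect a harmful effect of the new algorithm, and section 3.3 aims at policy and wider implementation. A safety result from watched consultations answers a narrower question, and an observer effect cannot be removed from the data afterwards.

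**Working it through.** **Where the two components differ.**

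| Feature | Adherence study (1920) | Safety study (2160) |
|---|---|---|
| Observer in the consultation, scoring IMCI steps | yes | yes, same sentence |
| Expert repeats the assessment and may change the prescription | yes | not listed |
| Caretaker interview straight after the consultation | yes | not listed; understanding is tested at follow-up |
| Provider adherence is an outcome | yes | no |

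So one controlling condition is shared, and the most direct one, expert correction of treatment, is not.

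**The plan's own figure.** Inputs from the sample size section: 0.12 in all arms, margin 0.05, power 80%, 10% loss, 720 per arm. No significance level is given for this test.

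- One-sided 0.025: n = 2 × 0.12 × 0.88 × (1.96 + 0.8416)² / 0.05² = 664 per arm. With 10% loss this is 664/0.9 = 738, or 664 × 1.1 = 731. Both are within 3% of 720.
- One-sided 0.05: 523 per arm, or 576 to 582 with loss. This does not reproduce 720.

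The check below therefore uses one-sided 0.025 and 720 × 0.9 = 648 evaluable per arm. With equal rates of 12% the power is then 79.1%. Clustering is left out, as it is in this reproduction.

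**Illustration of an observer effect.** Assume, beyond the documents, that without an observer the new algorithm is inferior exactly at the margin: 12% against 17%. For observed rates p_C and p_T,

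SE = √{[p_C(1 − p_C) + p_T(1 − p_T)] / 648}

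P(declare non-inferiority) = Φ[(0.05 − (p_T − p_C)) / SE − 1.96]

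| Assumed effect of observation | p_C, p_T | SE | P(declare non-inferiority) |
|---|---|---|---|
| None | 12%, 17% | 0.0195 | 2.5% |
| Removes a quarter of the excess | 12%, 15.75% | 0.0192 | 9.5% |
| Removes half of the excess | 12%, 14.5% | 0.0188 | 26.4% |
| Lowers both rates by 10% | 10.8%, 15.3% | 0.0187 | 4.5% |
| Lowers both rates by 50% | 6%, 8.5% | 0.0144 | 41.2% |
| Widens the excess to 6 points | 12%, 18% | 0.0198 | 0.7% |

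Worked line, half removed: SE = √[(0.1056 + 0.1240)/648] = 0.0188; 0.025/0.0188 − 1.96 = −0.63; Φ = 0.264. At one-sided 0.05 the same case goes from 5% to 38%.

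The effect sizes in the first column are assumptions; the protocol gives no figure for any of them.

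**The case against.** **The separation still does its job.** A reader might infer that the safety sample is fully back under the conditions it was created to avoid. The protocol does not support that. Only the adherence-study procedures list the expert who repeats the assessment and may change the prescription. That is the most direct reason for fewer bad outcomes there, and the protocol never says that the observer is what makes conditions controlled. Section 2.5.2.5 repeats the expert rule in general terms, but no expert appears in the safety procedures. This objection stands and limits the point to one shared condition.

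**The direction is not fixed.** A reader might also infer a certain bias towards non-inferiority. Observation occurs in all three arms. It may improve care in the control arm, which makes non-inferiority harder to show. The new algorithm aims to reduce drug use, and the protocol cites 99% antibiotic prescription in malaria-negative febrile children (section 2.1.2). Closer adherence under observation could therefore widen the contrast and expose harm. This also stands. What remains is the protocol's own statement that controlled conditions make unfavourable outcomes less likely; with an absolute margin, that points towards non-inferiority.

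**The task table is thin evidence.** Its safety line is one short entry that also omits enrolment and the recording of treatment, so its silence does not prove that observation was unintended. It agrees with the wording for the 1920 consultations, but the contradiction does not depend on it: it lies within the safety section itself.

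**Conclusion.** The contradiction is real: the stated reason for a separate safety sample and the procedures for that sample do not fit together. The rationale is weakened, not voided. The probable consequence is some pull towards non-inferiority, and a safety conclusion that applies to observed rather than routine use.

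Its size is unknown. Across the assumed scenarios, the chance of declaring non-inferiority at a true unobserved 12% against 17% runs from 0.7% to 41%, against 2.5% with no observer effect. None of these values is an estimate for this trial. All rest on one-sided 0.025, 648 evaluable per arm and no clustering. The 720 per arm is not in dispute on this point. The text should be reconciled before enrolment, as a cheap improvement; the point does not invalidate the comparison.

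**What to change.** In the safety-study procedures, delete the in-room observer and the scoring of IMCI steps. Record the diagnosis classification and the treatment given, which the same paragraph already requires, after the consultation from facility records or the prescription and from the caretaker. This keeps the secondary outcome on drugs prescribed. Keep observation in the 1920-consultation study, in line with section 2.6.

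Cost: one protocol paragraph, and up to 2160 fewer observed consultations. The downside is that there are no step-by-step provider adherence data on the safety children, which is not an outcome of that component, and that classification data may be less complete.

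If the observer is kept, give the reason, withdraw the stated rationale for separate samples as it stands, and limit the safety conclusion to observed use.

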### **Sample size calculation**

**Appropriateness of drug use, provider's adherence and mothers' understanding of prescribed advice (objectives 3, 4 and 7):** The feasibility and adherence study will include 1920 patients (640 per arm). For objectives 3 and 4, this sample size is adequate to detect a significant difference between each arm on the rate of antibiotic prescription assuming that among malaria negative patients (80% of all), 60% will be prescribed antibiotics in the control arm versus 30% in those using the new protocol (intervention groups). For objective 7, this provides 80% power to detect a 20% difference in caretaker comprehension immediately after the clinic visit, at a 0.05 significance level. This large sample size is required taking into account the need for stratification by time period and setting (urban vs rural), as well as the potential heterogeneity due to the randomisation per health facility.

**Assessment of safety study and caretaker adherence to prescribed treatment and advice (objective 5 & 8):** The safety study will include another 2160 patients (720 per arm). This sample size is sufficient to demonstrate equivalence (non-inferiority) of the new algorithm when compared to old IMCI (or routine practice) on the primary outcome assuming a probability of 0.12 of unscheduled reattendance in all arms and an acceptable difference <0.05 (power 80%), with 10% loss of follow-up

(<http://www.ucalgary.ca/~patten/blackwelder.html>). An equivalence study has been chosen since we aim at achieving at least similar health outcomes but with less drug prescribed (antimalarials and antibiotics) with the new IMCI algorithm. The sample is also sufficient for 80% power to detect a 20% difference in caretaker actions one week after the clinic visit, at a 0.05 significance level.

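### After day 7 only uncured children are actively seen, so the between-arm rate of delayed complications rests on ascertainment that depends on day-7 cure

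*Protocol*

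**What the plan says.** The relevant text is in the Protocol, section 2.5.2, under the study of safety and caretaker adherence (objectives 5 and 8).

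- **Scheduled visits.** "The patient's caretaker will be asked to come back after 7 days, so that the child can be assessed for health outcome". Then: "If not cured at day 7, they will be reassessed at day 14". No later scheduled contact is described for a child rated cured.
- **Unscheduled contact.** Caretakers are "advised to come back to health facility in case the child is not better or gets worse after 1 or 2 days", the interval varying with how ill the child is. Of children who do return, the protocol says: "They will be seen by dedicated staff and assessed clinically in case of unscheduled reattendance or readmission". This is not restricted to uncured children, and no end date is given.
- **Contact details.** The diagnosis and treatment are recorded, "as well as a cell phone number if available". No later call is described.
- **Outcomes.** Two primary outcomes are named: unscheduled reattendance, and the share of caretakers who act on the advice given. The next sentence of the protocol reads: "Secondary outcomes will be the rate of patients cured at day 7, the rate of delayed complications and the rate of drug prescribed". The analytical plan in the same section compares outcomes between the two intervention groups and control.

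The sample size section plans 720 children per arm for this study, with 10% loss to follow-up.

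**The concern.** The new algorithm is meant to reduce antimalarial and antibiotic prescribing, and the safety study exists to show that doing so causes no harm. Section 2.5.2.5 justifies the control arm by the risk of overlooking a harmful effect of the algorithm, and section 3.5 rests the do-no-harm argument on this assessment. A child who looks well at day 7 and worsens afterwards is an obvious candidate for a delayed complication, and this is the child for whom nothing is scheduled after day 7.

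Two errors can follow. If late events in recovered children are missed in all arms, a real difference is diluted, and in a study that aims to show equivalence dilution favours the desired conclusion. If day-7 cure differs between arms, the arm with more uncured children is examined more closely after day 7 and may appear to have more late complications for that reason.

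**Working it through.** **The plan's own figure.** The safety sample size uses a reattendance probability of 0.12 in all arms, a margin of 0.05 and 80% power. The alpha is not stated; I assume one-sided 0.025.

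n = 2 × 0.12 × 0.88 × (1.960 + 0.842)² / 0.05² = 664 per arm.

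Allowing for 10% loss gives 664/0.9 = 738, or 664 × 1.1 = 731, both within 3% of the planned 720. The present point does not alter that figure. It concerns how events are found among the 720 × 0.9 = 648 evaluable children per arm.

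**Who is actively seen after day 7.** The protocol gives no day-7 cure rate, so 80% to 95% is assumed.

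- Cured, nothing scheduled after day 7: 648 × cure rate.
- Uncured, seen at day 14: 648 × (1 − cure rate).

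**What could be missed.** The protocol gives no complication rate either. Assume a day 8–14 risk of 1% in cured and 5% in uncured children, that the day-14 visit finds every event in uncured children, and that a fraction s of events in cured children is found because the child returns.

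True rate = cure × 1% + (1 − cure) × 5%

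Observed rate = s × cure × 1% + (1 − cure) × 5%

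Share missed = 1 − observed/true

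| Day-7 cure | Nothing scheduled after day 7 | Seen at day 14 | Missed, s = 0 | Missed, s = 0.5 | Missed, s = 1 |
|---|---|---|---|---|---|
| 80% | 518 | 130 | 44% | 22% | 0% |
| 90% | 583 | 65 | 64% | 32% | 0% |
| 95% | 616 | 32 | 79% | 40% | 0% |

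Other assumed risks give a similar picture. With 0.5% and 3%, 40% to 76% are missed at s = 0 and 20% to 38% at s = 0.5. With 2% and 5%, the ranges are 62% to 88% and 31% to 44%.

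**Effect on the comparison of arms.**

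1. *Different cure rates, same risk within each cure group (1% and 5%).* With 80% cure in one arm and 90% in another, the true rates are 1.8% and 1.4%, a ratio of 1.3. At s = 0 the observed rates are 1.0% and 0.5%, a ratio of 2.0. At s = 0.5 they are 1.4% and 0.95%, a ratio of 1.5.
2. *Same cure rate (90%), with risk in cured children doubled from 1% to 2% in one arm.* The true rates are 1.4% and 2.3%, a difference of 0.9 points. At s = 0 the observed rates are 0.5% in both arms and the harm disappears. At s = 0.5 they are 0.95% and 1.4%, half the true difference.

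The distortion can therefore go in either direction, and its size turns on s, which the protocol gives no means of estimating.

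**The case against.** The strongest reply is that there is a second route to late events. Any child with an unscheduled reattendance or readmission is assessed by dedicated staff, without a restriction to uncured children and without a day-7 cut-off. A reader might infer from the visit schedule that complications cannot be measured at all in recovered children, or that the 80% to 95% who are cured contribute nothing to the outcome. The protocol does not support either inference: a recovered child who relapses on day 10 and returns can be counted, and with full passive capture nothing is missed.

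This reply stands, but it does not remove the problem. Passive capture misses the child who goes elsewhere, does not return or dies at home. The advice to return concerns a child who is not better or gets worse within a day or two, and nothing addresses relapse after recovery. Return may also differ by arm through the intervention itself, because the electronic arm is designed to improve caretakers' understanding and adherence, and the candidate measures in section 2.5.2.1 include messages after the mother has left the clinic.

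A second reply is that the meaning of delayed, and the analysis window, may be set in a statistical analysis plan that is not at hand. That is fair as to definitions, and the absence of a definition here is not the fault. But an analysis plan cannot recover day-14 status that was never collected, and the visit rule is fixed in the protocol.

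**Conclusion.** The point holds for one secondary safety outcome. Active ascertainment after day 7 is conditional on day-7 cure, so a between-arm rate of delayed complications that includes day-14 findings does not compare like with like. If 80% to 95% are cured, about 130 to 32 of 648 children per arm are actively seen after day 7. The share of late events missed cannot be given as one figure: under the 1% and 5% risks it runs from none with full passive capture, through 22% to 40% with half, to 44% to 79% with no passive capture. The cure rates, risks and capture fractions are all assumptions.

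A reader might go further and infer that the primary outcome mixes 7-day and 14-day exposure. If 20% were uncured in one arm and 10% in another, mean scheduled observation would be 7 + 7 × 0.20 = 8.4 days against 7 + 7 × 0.10 = 7.7 days, 9% more. The documents do not support reading this as bias in the primary outcome. Nothing ties the counting of unscheduled reattendance to the visit schedule, the passive route is open to every child, and the return advice suggests that many reattendances would come early. What remains for the primary outcome is that it should be counted over one window that is the same for all children.

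**What to change.** 1. State one window, in days from enrolment, over which both unscheduled reattendance and complications are counted for every child whatever the day-7 result, and say what counts as a delayed complication. Closing the window at day 7 is the simplest choice but discards later reattendances. A longer window keeps them, on passive capture only.
2. Base the between-arm comparison only on events ascertained in the same way in every child: the day-7 assessment plus unscheduled reattendance or readmission within the window.
3. Report what is found at the scheduled day-14 visit descriptively, under the name *complications by day 14 among children not cured at day 7*, and draw no whole-sample safety conclusion about delayed complications from it.

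These changes are wording only. They need no extra visits and leave the sample size as it is.

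Optionally, obtain day-14 status for all children by calling the phone numbers already recorded. This would allow a real comparison of late complications. It costs one additional call per child with a number, and coverage would be incomplete because numbers are recorded only where available. Coverage should then be reported by arm and by urban or rural setting.
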